### Eligibility criteria {10}

All undergraduate students at the participating universities that are at least 18 years of age and who screen positive for elevated depressive and/or anxious symptomatology will be eligible to participate irrespective of whether they also present symptomatology of other CMDs like adult ADHD, substance use disorders, and PTSD. Exclusion criteria include any one of the following: (1) screening positive for possible bipolar disorder, (2) report having received a diagnosis of psychosis, or (3) are considered to have serious suicide risk based on self-report of suicide ideation with current intent.

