### Outcomes {12}

The primary outcomes will be depression and anxiety symptom reduction and remission at 90 days and 12 months measured by the widely-used Patient Health Questionnaire-9 (PHQ-9) [44], Generalized Anxiety Disorder-7 Scale (GAD-7) [45], and the PHQ-Anxiety and Depression Scale (PHQ-ADS) [46]. The PHQ-9 is a self-report measure of depressive symptoms in the prior 2 weeks. Scores range from 0 to 27 with higher scores representing greater depressive symptomatology. The scale has both a sensitivity and specificity of 88% for identifying MDD [44]. The GAD-7 is a self-report measure of anxiety symptoms in the prior 2 weeks. Scores range from 0 to 21 with higher scores representing greater anxiety. Sensitivity and specificity for identifying GAD range from 70 to 92% [47]. The PHQ-ADS is a composite measure of the PHQ-9 and the GAD-7. Primary outcomes will be assessed both dimensionally and categorically. Consistent with standard practice, categorical thresholds for treatment response will be outcome scores less than 50% of baseline scores [48]. Remission will be defined as 0–4 on the PHQ-9 [49], 0–4 on the GAD-7 [45], and 0–9 on the PHQ-ADS [46].

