##### (ii) CMDs

MDD and GAD will be the primary foci of the intervention. The assessments of the primary outcome disorders will be the widely used PHQ-9 (depression) [44] and GAD-7 (anxiety) [45] scales. Clinical thresholds will be scores of 10+ on the PHQ-9 [65], 10+ on the GAD-7 [45], and 20+ on the recently-developed PHQ-ADS [46]. Eligibility for the trial will require students either to meet criteria for one or both of these disorders or of the PHQ-ADS. However, we will also evaluate other DSM-5 disorders: panic disorder, social phobia, binge eating disorder either with or without purging, PTSD, insomnia, bipolar disorder, adult ADHD, and frequency and quantity of alcohol and drug use (cannabis, cocaine, any other street drug, or a prescription drug either used without a prescription or used more than prescribed to get high, buzzed, or numbed out). Although a larger set of disorders is used in the face-to-face WMH surveys [66], the 9 in the WMH-ICS surveys include those associated with highest role impairment among college students [1]. Bipolar disorder will be assessed with the CIDI-SC [51, 52, 67] only for lifetime prevalence and, as noted above, will be exclusionary for the trial. We will also ask if they have ever been diagnosed with schizophrenia or psychosis as an exclusionary criterion. The other 8 disorders will be assessed either for lifetime (binge-purging disorders), 2-week (PHQ-9, GAD-7), 6-month (ADHD), or 30-day (the other disorders) prevalence. The baseline survey will also assess lifetime prevalence and course of GAD, MDD, and PTSD based on these being hypothesized prescriptive predictors of treatment response (Table 2). Panic disorder will be assessed with the CIDI-SC [51, 52], social phobia with DSM-5 diagnostic criteria [53], binge/purge with the PRIME-MD PHQ [54], PTSD with the six-item short-form PCL-5 screening scale [55], insomnia with a reduced version of the ISI [56], and ADHD with the Adult Self-Report Scale-V1.1 (ASRS-V1.1) [68] screener. Modified versions of the C-SSRS [57] and the SITBI [58] will also be used to assess suicidal ideation, plans, and attempts. As noted above, suicidality with intent (i.e., a current suicide plan with intent to act on the plan) will be exclusionary for the trial.

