## Statistical methods

### Statistical methods for primary and secondary outcomes {20a}

#### Analysis of aggregate intervention effects

Aggregate differences in outcomes across arms will be estimated using an intent-to-treat (ITT) [75] analysis approach as well as using a complier average causal effect (CACE) [76] analysis approach. ITT estimates the impact of intervention among all students offered the intervention whether or not they participated. CACE, in comparison, estimates the impact of intervention only on the students who participated in iCBT. To estimate CACE, we will use two-stage least squares (2SLS) [77] and control function procedures [78]. To test the validity of the instrumental variable (IV) assumption in 2SLQ, we will assess balance in the covariate distributions across groups generated by the IV. We will also conduct sensitivity analyses to detect violations of the “independence to unmeasured confounders” assumption, the “exclusion restriction” assumption, and the “monotonicity” assumption as described by Baiocchi et al. [79]. Inverse probability weights (IPW) will be used in all these analyses to deal with loss to follow-up [80].

For each of the two outcome assessments (i.e., 90-day and 12-month), probability of a student being in the study at time *t* will be calculated conditional on information collected as of time *t − 1*. Flexible, nonparametric estimation methods will be used for confounder control [81]. The IPW as of time *t* will be based on the product of these conditional probabilities up through *t*. The treatment-specific mean outcome will be estimated using these weights for the individuals whose outcomes were observed at *t*. Under a coarsening at random assumption, this estimator converges with increasing sample size to the treatment-arm-specific mean outcome that would have been observed had all individuals remained in the study up through *t* [82]. This assumption is closely related to the strong ignorability assumption commonly used in observational studies [83]. Generalized linear models (GLMs) will be used to estimate ITT effects on continuous outcomes, making use of standard visual diagnostics to choose appropriate link functions and error structures [84].

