We will report adjusted mean differences (AMDs) with design-adjusted 95% CIs (confidence intervals) and use Poisson regression with robust variance estimation for binary outcomes and report adjusted prevalence ratios (aPRs) with 95% CIs. We will calculate numbers needed to treat (NNTs). When data are missing, we will provide thorough summaries of reasons for missingness and proportions of missing data, test for differences in the characteristics of patients with and without missing data, and describe these and the implications of missing data for interpretation when we report results. As our IPW approach to missing outcomes data will be based on a missing-at-random (MAR) assumption, sensitivity analysis will be carried out based on the weaker missing-not-at-random (MNAR) assumption using pattern mixture modeling [85] in a generalized mixed model framework [86]. The predictors of success in obtaining outcome data at time *t* will include information obtained in prior waves of data collection along with data on intensity of efforts needed to obtain outcome data in a discrete-time survival framework (i.e., in response to the 1^st^, 2^nd^, or 3^rd^ telephone attempts). A range of assumptions about the distribution of the missing data will be made in this approach to investigate sensitivity of results [87]. We will record and report distributions and correlates of dropout and account for all patients in reports.

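### PHQ-9 and GAD-7 remission and response carry no baseline condition although one elevated scale suffices for entry, which inflates single-scale remission rates and dilutes prevalence ratios and NNTs

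*Protocol article*

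**What the plan says.** Outcomes {12} of the protocol article names the endpoints: "The primary outcomes will be depression and anxiety symptom reduction and remission at 90 days and 12 months". It then gives the cut-offs: "Remission will be defined as 0–4 on the PHQ-9 [49], 0–4 on the GAD-7 [45], and 0–9 on the PHQ-ADS [46". Response is relative to the student's own starting score: "categorical thresholds for treatment response will be outcome scores less than 50% of baseline scores". Neither definition sets a minimum baseline score.

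Entry is wider than either scale alone. Section (ii) CMDs gives the thresholds ("Clinical thresholds will be scores of 10+ on the PHQ-9 [65], 10+ on the GAD-7 [45], and 20+ on the recently-developed PHQ-ADS [46") and the rule: "Eligibility for the trial will require students either to meet criteria for one or both of these disorders or of the PHQ-ADS". Eligibility criteria {10} agrees, admitting students "who screen positive for elevated depressive and/or anxious symptomatology will be eligible to participate".

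Under Analysis of aggregate intervention effects, "ITT estimates the impact of intervention among all students offered the intervention whether or not they participated". For binary endpoints the plan will "use Poisson regression with robust variance estimation for binary outcomes and report adjusted prevalence ratios (aPRs) with 95% CIs", and NNTs will be calculated. No sentence limits a scale's remission or response to students elevated on that scale at baseline.

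**The concern.** Remission on a scale has meaning for a student who was ill on that scale. Here a student admitted for depression may have almost no anxiety symptoms, or the reverse. If that student stays where they started, the stated definition records a remission in whichever arm they are in.

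Response errs the other way. With a baseline of 0 no follow-up score is below half of it, and with a baseline of 1 only a 0 qualifies. The same stable, symptom-free student is thus a remitter on one categorical outcome and a non-responder on the other.

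The stake is how the trial's categorical primary results can be read. Adding a similar number of remitters without a treatment contrast to each arm raises every remission rate, pulls the prevalence ratio towards 1 and raises the NNT. The resulting rates no longer compare with the remission rates that the sample size section takes from earlier iCBT trials.

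**Working it through.** **The plan's own figure.** Sample size {14} states that fewer than 150 per arm suffice for the aggregate effects (remission about 30% vs half that, 80% power, two-sided 5%). The pooled two-proportion formula gives 121 per arm for 30% vs 15%. Inflated by 1/(1 − d) for loss to follow-up, this is 135 at d = 10%, 143 at 15% and 150 at 19%. The statement reproduces for losses up to about 18%, so the aggregate calculation itself is sound.

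**Which eligible students already meet remission?** PHQ-9 runs 0–27 and GAD-7 runs 0–21. The entry rule is PHQ-9 ≥ 10, or GAD-7 ≥ 10, or a total ≥ 20. The third route adds nobody, because two scores of at most 9 sum to at most 18. Listing all score pairs (possible pairs, not students):

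- eligible pairs: 516
- with GAD-7 0–4: 18 PHQ-9 values (10–27) × 5 = 90
- with PHQ-9 0–4: 12 GAD-7 values (10–21) × 5 = 60
- with both at 0–4: none
- lowest eligible PHQ-ADS total: 10 + 0 = 10, so none is in the 0–9 remission range
- response impossible: 18 pairs with GAD-7 = 0 and 12 with PHQ-9 = 0

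**Size of the dilution.** Inputs from the protocol: remission 27.5% vs 17.5% (the simulation in Sample size {14}). Assumed, because the documents give neither: a share q already at 0–4 at baseline, and a proportion s of them still at 0–4 at follow-up in every arm. With s = 0.75, the observed rate in an arm is (1 − q) × p + q × s.

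For q = 20%: iCBT 0.8 × 0.275 + 0.2 × 0.75 = 0.37; control 0.8 × 0.175 + 0.2 × 0.75 = 0.29. The difference is 0.08, the ratio 0.37/0.29 = 1.28 and the NNT 1/0.08 = 12.5.

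| q | iCBT | Control | Ratio | NNT | Control remitters already at 0–4 at baseline |
|---|---|---|---|---|---|
| 0% | 27.5% | 17.5% | 1.57 | 10.0 | 0% |
| 10% | 32.25% | 23.25% | 1.39 | 11.1 | 0.075/0.2325 = 32% |
| 20% | 37.0% | 29.0% | 1.28 | 12.5 | 0.15/0.29 = 52% |
| 30% | 41.75% | 34.75% | 1.20 | 14.3 | 0.225/0.3475 = 65% |

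Varying s from 0.6 to 1.0 at q = 20% moves the ratio only between 1.31 and 1.24. The NNT stays at 12.5, since s cancels from the difference.

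**The case against.** **The denominator may be in the unseen SAP.** The outcomes section gives cut-offs rather than denominators, the intent-to-treat sentence is written to contrast with the complier analysis, and the sample size section speaks of episode remission, which presupposes an episode. This has some force, and a later document may well restrict the denominators. But the article defines a primary outcome and an all-offered analysis population without restriction, and following it as written gives the results above.

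**A joint definition may be meant.** If remission required all three criteria at once, nobody would meet it at baseline. But PHQ-9 ≤ 4 and GAD-7 ≤ 4 already imply a total of at most 8, so the 0–9 criterion would be redundant. The per-scale reading fits better; if the joint one is meant, the text should say so.

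**The size is assumed.** This stands. The Background says comorbidity is highly prevalent in this population, which argues against a large share at 0–4 on the other scale. Nor is detection necessarily lost: with 30% vs 15% among the rest and s = 0.75, power at 500 per arm stays above 0.99, at 0.98 and at 0.93 for shares of 10%, 20% and 30%.

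**Stronger readings the documents do not support:**

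- *All categorical primary outcomes are affected.* PHQ-ADS remission is not.
- *Every student starting at 0–4 is a remitter.* Only those at 0–4 at follow-up are.
- *The PTR would profit from predicting baseline status.* The heterogeneity section says the method estimates treatment contrasts directly and judges the rule by its gain over balanced randomization. Students with the same outcome in every arm add nothing to that gain; they can only dilute it.
- *Restricting to elevated students raises power.* At 27.5% vs 17.5%, power is 0.93 with 400 per arm, but 400 is what remains at q = 20% after removing only scores of 0–4. A 10+ restriction also removes scores of 5–9, whose share is unknown. With 300 per arm power is 0.84, and with 200 it is 0.67, against 0.77 for the diluted analysis of all 500 at q = 20%.

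**Conclusion.** The point holds for PHQ-9 and GAD-7 remission and response, and not for PHQ-ADS remission. As written, the definitions and the entry rule together let students who were never elevated on a scale count as remitters on it, and make response unattainable from a baseline of 0.

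The direction is certain if any eligible students start at 0–4, remain there equally often in every arm, and iCBT raises remission in the rest: higher rates everywhere, ratios closer to 1, larger NNTs. The amount is not certain. Over shares of 10% to 30%, the illustrated ratio falls from 1.57 to between 1.39 and 1.20, and the NNT rises from 10 to between 11.1 and 14.3. These figures rest on an assumed share, an assumed 75% persistence and no treatment contrast in that group. Randomization stratified by both severities guards against imbalance between arms, but not against this dilution. The wording should be changed before the categorical results are analysed.

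**What to change.** - Define PHQ-9 remission and response among students with baseline PHQ-9 of 10+, and GAD-7 remission and response among students with baseline GAD-7 of 10+. Both subsets are fixed by baseline scores, so they remain randomized comparisons.
- For all randomized students, and as the target of the PTR, name one remission outcome that nobody meets at baseline: the existing PHQ-ADS remission, or remission on every scale elevated at baseline.
- Keep the continuous scores in all students, adjusted for baseline.
- State that the three remission criteria are separate outcomes, if that is intended.

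The cost is wording in the protocol and SAP, with no new data. The single-scale binary analyses lose students scoring 0–9 on that scale. Their power may rise or fall depending on the unknown share at 5–9, so the baseline score distribution should be tabulated and reported with these results.

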### Participant timeline {13}

The participant timeline for each of the three trials is outlined in Fig. 1. Once students are identified through one of the three recruiting methods, they will be sent through email the study invitation, consent form, and baseline survey. Those who are not eligible to participate will be followed up by the clinical liaison at their university and provided the appropriate treatment. Those who are eligible will be randomized to one of the three treatment arms and will subsequently be asked to complete follow-up surveys at 90 days and 12 months after randomization. In the second- and third-year trials, participant flow is similar except that 25% of eligible participants will be randomized according to the PTR generated from the first-year pragmatic trial short-term and long-term effects in years 2 and 3 respectively and the remaining 75% will be randomized with equal allocation into the three treatment arms. The schedule of enrollment, intervention, and assessments for the three trials is outlined in Fig. 2.

**Fig. 1 Fig1:**
[figure not shown]
Participant timeline

**Fig. 2 Fig2:**
[figure not shown]
Schedule of enrollment, intervention, and assessments for pragmatic trials 1, 2, and 3

### Sample size {14}

#### Expected number of subjects

We expect to randomize at least 1500 participants in the first year trial and 1000 in each of the second and third year trials.

#### Expected effect size and power calculations

We powered the study to estimate heterogeneity of treatment effects as defined by the increase in the proportion of patients we would expect to remit from the primary outcomes based on optimized rather than randomized treatment of 5%. We considered this the minimum difference of interest. Although we will be interested both in continuous (i.e., differences in mean scores on symptom rating scales) and categorical (i.e., probabilities of treatment response and remission) outcomes, we evaluated statistical power for a categorical measure of episode remission because this is of greatest clinical importance and because larger samples are required for powerful detection of effects on categorical than continuous outcomes. Meta-analyses of previous iCBT trials for CMDs show that treatment response is approximately 50% and remission is approximately 30%, with rates roughly half these values for control conditions. Closed-form solutions show that samples with fewer than 150 patients per arm provide adequate statistical power (.8 power based on .05-level two-sided tests) to detect effect sizes this large even after making reasonable adjustments for loss to follow-up. However, estimating power to detect heterogeneity of treatment effects is more complex because closed-form solutions do not exist and simulation is needed to determine required sample sizes.

We carried out such a simulation by building a series of hypothetical population models that assumed that each patient was randomized either to iCBT or a control condition; that the aggregate remission rates after adjusting for loss to follow-up were 27.5% and 17.5% in the two treatment arms, respectively; and that a series of relatively complex nonlinear-interactive multivariate associations existed between 20 predictors and remission. The assumed distributions of predictors and interaction values among predictors were consistent with those found in previous studies. We varied these coefficient values in different models to maintain the same aggregate remission rates but to have the difference between remission rates based on randomized versus optimized treatment vary between 0 and 15%. In each model, the remission rate if intervention assignment was randomized was set at 10% (i.e., 27.5–17.5%), but the remission rate if intervention assignment was optimized (i.e., if each student who would have a better outcome if assigned to iCBT was, in fact, assigned to iCBT and all other students were assigned to the control condition, which in some cases could involve these students receiving treatment at the student clinic and having better outcomes than if they received iCBT) was varied between 0 and 15%. We used a state-of-the-art ensemble machine learning method detailed in the proposal to estimate heterogeneity of treatment response. We discovered that adequate statistical power (again defined as .8 power based on .05-level two-sided tests) to detect a difference between the two remission rates of 5%, which we considered the minimum difference of interest, would require a sample of at least 500 patients per treatment arm [59]. A difference of 5% would represent a 50% increase on the 10% aggregate base of the difference in the remission rate between intervention and control groups. Based on a review of previous precision treatment analyses of CMDs, a difference of this magnitude is plausible. Based on this result, we designed the study to have a sample size of 500 per treatment arm. As noted above in the discussion of the sample design, we will have 1500 eligible students to randomize across three arms in the first trial, making it possible for us to estimate a precision treatment model based on data obtained in this trial. However, as noted above in the section on study design, the 12-month follow-up data for these students will not be available until YR2 and it will be possible to use the results of the model for the trial 2 randomization for the first time in YR3. We will replicate the model with follow-up data for students randomized in YR2 and use the harmonized precision treatment model results obtained in YR3 for a final Trial in YR4.

### Recruitment {15}

There are three avenues of recruitment. The first is from the student mental health clinics. When students request an appointment for the health clinic, the person responsible for appointments and intake will identify potential participants, describe the study, answer questions, and provide to the study team the contact information for interested students. The second is from a list that university officials will provide of all enrolled undergraduate students. Each week a random sample of students will be sent an email saying that their university is concerned about the emotional wellbeing of their students, describing the study, and providing a personalized link to further information, the informed consent, and baseline survey. They will also be given contact information and can request a call if they want to ask questions or need further information. A third, and final, avenue of recruitment is through postings on the universities’ social media. Potential participants are told to send an email to request further information or obtain a link to the study.

## Assignment of interventions: allocation

### Sequence generation {16a}

Baseline survey results will be used to stratify randomization of eligible patients across study arms. This will be done automatically within the Qualtrics survey platform using the 3-way cross-classification of sex at birth, depression symptom severity and anxiety symptom severity.

### Concealment mechanism {16b}

The allocation is concealed in that the allocation sequence is automatically generated in the Qualtrics platform and simultaneous with assignment.

### Implementation {16c}

The allocation sequence will automatically be generated in the Qualtrics platform at the end of the baseline survey, and a screen will show participants to which group he or she has been assigned. Simultaneously, the Qualtrics platform will send an automatic message to the iCBT coordinator (in the case of participants assigned to iCBT) who will then send out instructions to access the iCBT intervention or in the case of participants assigned to TAU the Qualtrics platform will send out an automatic message to the university clinical liaison.

